## Subjects and methods

### Subjects

Our study will compare data collected in patients with moderate to severe MDD (“currently depressed group”, *n* = 20) treated unsuccessfully with classical antidepressants (SSRIs, SNRIs) before the initiation of a new antidepressant treatment according to good practice recommendations, with those included in two other study groups, comprising:
- non-depressed healthy volunteers (“control group”, *n* = 20), which enables us to control both the depression factor and the treatment factor for the characterization of neuroinflammation. They will be matched on age and gender to the experimental group of currently depressed patients;- depressed patients reaching clinical remission (“remitted depressed group”, *n* = 20) and still being treated with antidepressants, which allows us to control the depression factor. We hypothesize that the presence of an effective antidepressant treatment will contribute to demonstrate a significant decrease in neuroinflammation in those depressed patients. This group will be matched to the currently depressed group according to the class of antidepressant treatments (SSRIs, SNRIs), as well as age and gender.

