Patients with any of the following conditions are not eligible for both the currently depressed and remitted depressed groups: (1) woman who is pregnant (test at enrolment), parturient, or lactating, (2) persons deprived of their liberty by judicial or administrative decision, (3) persons unable to express consent, (4) subjects with an identified neurodegenerative condition or a psychiatric pathology other than MDD (bipolar disorder, chronic psychotic disorder, addictive disorder except for nicotine, obsessive-compulsive disorder, post-traumatic stress disorder), (5) subjects with a history of stroke, (6) subjects with an acute infectious pathology, or chronic or acute inflammatory diseases, (7) subjects with a history of autoimmune diseases, (8) subjects receiving long-term anti-inflammatory and immunosuppressive therapy, (9) subjects with antipsychotic treatment in the last 3 weeks prior to enrolment, (10) subjects with a prescription of diazepam, midazolam, chlordiazepoxide in the last week prior to enrolment, (11) subjects with contraindications to MRI or PET imaging, (12) subjects who refuse to be informed of an abnormality detected during MRI examination.

The exclusion criteria for the control group are: (1) a significant history of psychiatric or somatic disorders, (2) a current mental disorder, (3) an active suicidal risk, (4) an ongoing psychotropic treatment.

Depressed patients will be recruited throughout 4 centers (Bordeaux, Montpellier, Tours, and Toulouse) of the French network from 13 expert centers for resistant depression (50). The subjects of the control group will be included at clinical investigation sites working locally in close collaboration with each participating expert center.

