### PET assessment

The ^18^F-DPA-714 and ^18^F-FEPPA molecules are two second radiotracers that target TSPO (overexpressed microglial receptor with inflammation) (55, 56). These two tracers cross the blood-brain barrier (BBB) and have a good affinity for TSPO (57, 58). The ^18^F-DPA-714 tracer is metabolized rapidly and some metabolites secondary to oxidation can cross the BBB in small amounts (59). The FEPPA tracer is also metabolized but its hydrophile metabolites do not cross the BBB (57). The amounts of injected activity and the effective patient dose are comparable between the two tracers (47, 60–62). The ^18^F-DPA-714 tracer has been studied extensively in humans as well as in preclinical models (51 references on Medline) (46–49). There is less information on the use of FEPPA (14 references on Medline, only 8 clinical studies).

Articles on the FEPPA use in humans mention an acquisition time of 125 min, which is difficult to achieve with a large number of subjects and is very uncomfortable for patients who must be immobile during these 125 min. For FEPPA, the data analysis is performed on a kinetic model with two compartments and arterial blood samples must be collected from the patient to measure the input function of the radiotracer (62). The main advantage of using ^18^F-DPA-714 is its acquisition and analysis protocol. The radiotracer is injected (200 MBq) and then a 30-min acquisition is performed 1 h after the injection. The analysis consists of calculating a standardized uptake value (SUV). Some studies have shown that using this semi-quantitative analysis method and using a reference region results in less variability than studies using a kinetic model (49). Since ^18^F-DPA-714 appears to be the preferred tracer for studying neuroinflammation on PET, it will be used in this study.

In addition, there is known a genetic polymorphism for TSPO. This polymorphism determines the tracer′s affinity for TSPO, with some persons having high affinity sites, mixed affinity sites or lower affinity sites. The two radiotracers (^18^F-DPA-714 and ^18^F-FEPPA) are both impacted by this genetic polymorphisms (63). For feasibility reasons, the TPSO genotype of subjects cannot be an inclusion criterion; nevertheless, this parameter will be taken into account during the data analysis as a covariate, allowing us to weigh the PET imaging data based on whether the individuals have high or low affinity sites.

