### Experimental procedures (Table 1)

#### Preselection

Patients in both the currently depressed and remitted depressed groups will be preselected during their medical follow-up within each participating research site. Investigators will inform the patient and answer all questions about the purpose, nature of constraints, foreseeable risks, and expected benefits of the present research. They will also specify the rights of the patient regarding research and will verify the eligibility criteria. A copy of the Information/Consent form will then be given to the patient. Healthy volunteers for the control group will be invited by phone to participate into the study by a Clinical Investigation Centre clinical research associate. A copy of the information leaflet will be sent to them, giving them sufficient time to consider their participation.

**Table 1 T1:** Summary of INFLADEP design.

	**Preselection**	**Enrolment visit D0**	**Assessment visit D7 (± 5 days)**
Patient information	✓	✓	
Collection of informed consent		✓	
Clinical examination^1^ – Validation of eligibility criteria		✓	
Collection of blood samples^2^		✓	
MRI examination			✓
PET examination			✓
Questions about concomitant treatments		✓	✓
Search for AE/SAE		✓	✓

1 *Clinical examination: discussion with doctor, MADRS, BAS, C-SSCR, MINI surveys*.

2 *To measure CRP levels in healthy volunteers and biological markers (TNF-alpha, IL-6), TSPO phenotype in all subjects, beta-HCG for women of childbearing age*.

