#### Analysis of PET imaging data

To evaluate the brain kinetics of [18F] DPA-714, PET images will be co-recorded on the MNI atlas with PMOD® software. To construct time-activity curves of [18F] DPA-714, the PET images will be segmented into 13 regions of interest (ROI): precuneus, anterior cingulum, posterior, frontal, temporal, parietal, occipital cingulum, hippocampus, semi-oval centrum, anterior putamen, posterior putamen, caudate nucleus, and intersections, as defined in the MNI-AAL atlas. The binding potential (BP) is the ratio of B_max_ (receptor density) to KD (dissociation constant): BP = B_max_ / KD shall be calculated. Additionally, the distribution volume ratio (DVR) will be estimated from the region of interest and a reference region using, for example, Logan graphical analysis (66) with the cerebellum as reference region for the images obtained between 0 and 90 min (46). In this study, the DVR will be calculated as the slope of the linear part of the Logan analysis using PMOD software. We will calculate the BP for the 13 ROIs mentioned above, as well as for the entire brain.

For the primary hypothesis, PET data will be analyzed by multivariate ANOVA with TSPO Volume in the 13 ROIs as the dependent variables and diagnosis and genotype as fixed factors. Main effects will be considered significant at the conventional *P* ≤ 0.05. Effects in each region, will be analyzed by univariate ANOVA.

As a secondary analysis, a MANOVA including every brain region sampled (including all cortical and subcortical regions) will be performed to assess the effect of diagnosis on TSPO Volume. A partial correlation will be used in a secondary analysis to quantitate the relationship between TSPO Volume in the primary regions of interest and severity of symptoms of MDD measured by total MADRS score.

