#### Analysis of all data

PET and MRI imaging, clinical symptomatology and biological markers. PET and MRI images will be co-recorded using a method previously used by our team (71) [e.g., 71] so that the maps of all multimodal markers have the spatial consistency needed for their statistical comparison. Firstly, for each marker map, we will perform *t*-tests to compare the groups with each other (SPSS 25.0). This will allow us to quantify the structural, functional and inflammatory alterations that characterize each group (i.e., treatment-resistant MDD vs. control, responsive MDD vs. control, treatment-resistant MDD vs. responsive MDD). Secondly, we will verify that there is no spatial collocation between the atrophy marker (MRI) and the inflammation marker (DPA714 -PET) that can induce a different interpretation of PET results. Finally, we will correlate the inflammation marker maps with the structural and functional marker maps generated with MRI. This will allow us to understand whether neuroinflammation is linked to brain changes (e.g., iron deposits, functional alteration).

To study the correlation between the severity of depressive symptoms, suicide risk and the intensity of neuroinflammation, graphic representations will be made to observe the distribution of these data in the two groups concerned. The Pearson correlation coefficient will be calculated in each instance. The same analysis strategy will be used to measure the correlation between plasma concentrations of biological markers of peripheral inflammation and the intensity of neuroinflammation in the three study groups.

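### The pairwise t-tests on the PET maps omit the TSPO genotype that the protocol promises as a covariate, and so give a second, less precise answer to the primary question

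*Protocol article*

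**What the plan says.** - **Genotype is promised.** PET assessment explains that the TSPO polymorphism sets the tracer's affinity and that, for feasibility, the "genotype of subjects cannot be an inclusion criterion"; "nevertheless, this parameter will be taken into account during the data analysis as a covariate". The footnote to Table 1 has the enrolment blood sample provide "TSPO phenotype in all subjects", so the variable will be available.
- **The primary model includes it.** Analysis of PET imaging data specifies a MANOVA on 13 regions with "diagnosis and genotype as fixed factors", followed by univariate ANOVA per region.
- **The secondary MANOVA does not name it.** The same section plans a MANOVA over every sampled region to assess the effect of diagnosis. No other term is mentioned.
- **The pairwise comparisons have no covariate.** Analysis of all data plans t-tests between the groups for each marker map and states their purpose: "This will allow us to quantify the structural, functional and inflammatory alterations that characterize each group". The contrasts listed are treatment-resistant versus control, responsive versus control, and treatment-resistant versus responsive. The same section identifies the inflammation marker as the DPA-714 PET map.
- **Matching and centres.** Under Subjects, the article says of the controls: "They will be matched on age and gender to the experimental group of currently depressed patients". Remitted patients are matched on age, gender and antidepressant class. Patients come from four centres. None of the written group comparisons on PET measures names age, sex or centre.

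**The concern.** The article identifies one variable that affects the PET signal whatever the disease state, declines to control it at entry, and undertakes to handle it in the analysis. One set of group comparisons on that signal then has no place for it. That set includes treatment-resistant versus control, which is the primary contrast under Outcomes.

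Two things are at stake. First, the primary question gets two answers, one adjusted and one not, and nothing says which prevails if they differ. Second, with 20 subjects per group, variation due to genotype stays in the error term of the t-tests, so they are less precise than they need be. Age and sex, which the design matches on, and centre could be included in the same model and are not.

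**Working it through.** **1. The plan's own figure.** Study sample calculation states 80% power with 20 per group for 12.3 versus 9.3 ml/cm³, a difference of 3.0. It gives no SD, so the 80% cannot be reproduced and can only be inverted. For a two-sided t-test at 0.05 with 20 per group (38 df), the noncentral t gives 80% power at a standardised difference of d = 0.909, so SD = 3.0 / 0.909 = 3.30 ml/cm³. The normal approximation gives d = 0.886 and SD = 3.39.

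**2. Power lost by omitting genotype.** Assumptions, none of them in the article:
- the 80% refers to the genotype-adjusted comparison;
- two affinity classes, split 60/40 (p = 0.4);
- the classes differ by g residual SDs.

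With genotype omitted, the variance grows by the factor 1 + p(1−p)g², so d_unadjusted = 0.909 / √(1 + 0.24 g²).

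| g (SD) | variance factor | d without genotype | power, 20 per group |
|---|---|---|---|
| 0.5 | 1.06 | 0.883 | 77.7% |
| 1.0 | 1.24 | 0.816 | 71.1% |
| 1.5 | 1.54 | 0.733 | 61.7% |

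**3. How far the two answers could differ.** Chance imbalance in genotype moves the unadjusted group difference with an SD of g√(2p(1−p)/20) = g × 0.155, that is 0.08, 0.15 or 0.23 SD units for the three values of g. With a 60% high-affinity share, two groups of 20 differ by four or more such subjects with probability about 26% (27% at a 50% share). A difference of exactly 4/20 shifts the contrast by 0.2g, which is 0.1, 0.2 or 0.3 SD against the 0.909 planned on. This is the same variation that lowers the power in step 2, seen in a single realised trial. It is not an additional loss.

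**4. Type I error.** If genotype is independent of group, the omitted term is only noise, and the t-test estimates its SD from data containing that noise. Simulating the null with g = 0.5, 1.0 and 1.5 gives a rejection rate of 5% to within simulation error (4.9% to 5.2%). The test remains valid.

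**5. Cost of adjustment in degrees of freedom.** At d = 0.909 with no gain in variance, power is 80.0% on 38 df. Genotype in three classes leaves 36 df (79.9%). Age, sex and three terms for centre leave 31 df (79.5%). A model on all 60 subjects has 60 − 3 − 2 − 5 = 50 residual df.

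The 13-outcome MANOVA pays more. For two groups of 20 and three genotype classes the error df are 40 − 1 − 1 − 2 = 36, and the denominator df are 36 − 13 + 1 = 24. Five more covariates reduce this to 19. Before any gain in variance, power falls from 65% to 60% at an assumed squared Mahalanobis distance of 2, and from 85% to 81% at 3.

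**The case against.** The strongest reply is that the primary analysis already honours the promise. The MANOVA and its univariate follow-up contain genotype, and the 80% was claimed for the primary contrast, not for the later t-tests. That stands. It confines the fault to the pairwise comparisons and the secondary MANOVA, and makes the power figures an illustration.

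PET assessment also says that the covariate lets the investigators weight PET data by affinity, so weighted values might be what enters the t-tests. This is possible, but Analysis of all data describes no such weighting. At best the text is ambiguous and needs the same correction.

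This is a condensed article, and an unseen plan may add terms. That has force for age, sex and centre. It has less for genotype, because the t-tests are written out and would have to be overridden.

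A reader might infer more than the article supports:
- **That matching is wasted without age and sex in the model.** Matching balances those factors whatever model follows. Ignoring it makes an unpaired test conservative: simulated type I error is 0.040 to 0.007 for assumed within-pair correlations of 0.1 to 0.5. The article does not say whether matching is individual or by frequency.
- **That centre or scanner differences bias the contrast.** The number of scanners is not given, and controls come from sites working with each expert centre. With an assumed 12/8 versus 8/12 split over two scanners and an offset of 0.5 to 1.0 SD, simulated type I error is only 5.3% to 5.9%.
- **That the t-tests are the only analysis of the remitted group.** Neither MANOVA limits diagnosis to two levels.
- **That genotype imbalance produces false positives.** Step 4 of the working shows otherwise when genotype is unrelated to group.

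**Conclusion.** The point holds in limited form. The article promises genotype as a covariate, includes it in the primary MANOVA, and leaves it out of the pairwise t-tests on the PET maps and of the stated terms of the secondary MANOVA. The t-tests therefore conflict with PET assessment and give a second, less precise answer to the primary question.

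The loss is in power and precision. Nominal 80% becomes about 78%, 71% or 62% for assumed genotype effects of 0.5, 1.0 or 1.5 SD. These figures rest on the assumed 60/40 split, on an effect size inverted from the stated 80%, and on reading that 80% as adjusted power. If it was meant as unadjusted power, the same reasoning appears as a gain from adjustment instead, and the two should not be added. The contradiction itself rests on the text alone. The case for age, sex and centre is a weaker one, of efficiency only. The primary MANOVA is not undermined.

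**What to change.** 1. In Analysis of all data, replace the t-tests on PET measures with a linear model per region or map that yields all three pairwise contrasts. Include group and TSPO genotype, plus age and sex as matching factors. Add centre (or scanner, if more than one is used) only as a parsimonious term.
2. Name genotype as a factor in the secondary all-region MANOVA.
3. State that the primary contrast is judged by the primary MANOVA in Analysis of PET imaging data, and that the pairwise models are supportive.

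The change is to wording and needs no new data collection: genotype, age, sex and centre are known for every subject. It is not free. The additions beyond genotype take up to about five residual degrees of freedom in the univariate models (one for age, one for sex, three for four centres). They need not enter the 13-outcome primary MANOVA, where the same five cost more.

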## Introduction

Major depressive disorder (MDD) is a serious public health problem (1) with high lifetime prevalence (4.4-20%) in the general population (2). Impairment of quality of life is comparable to chronic diseases such as low back pain, high blood pressure, or cancer (3, 4). MDD is considered a “deactivation of psychosocial function” (5). It usually appears as part of a complex picture of comorbidities that are most often not or hardly managed since they may not be recognized (6). Standard therapeutic strategies often fail in up to one-third of cases in everyday clinical practice (7). The definition of treatment-resistant depression varies in the literature. Nevertheless, it is characterized by the absence of significant symptomatic remission after two successive attempts with antidepressants of different pharmacological classes, well-conducted in terms of dosage and duration, whilst ensuring quality observation (at least 80% of treatments made during the period under consideration) (8, 9).

The monoamine hypothesis is the most widespread aetiological theory of MDD (10, 11). Hence, all available antidepressants primarily act by increasing monoamine neurotransmission (serotonin, dopamine, and noradrenaline) (12). Consequently, hypofunction of the brain monoamine systems is among the most critical neurochemical mechanisms implied in MDD.

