### Eligibility criteria

The following inclusion criteria will be applied to all study groups: (1) men and women aged 25 to 55 years, (2) affiliated to a Social Security scheme, (3) able to understand the given instructions and information about the study design, and (4) have provided written informed consent. The currently depressed group will include patients: (1) meeting the DSM-5 criteria of MDD diagnosis, (2) experiencing significant depressive symptoms (as indicated by a score > 20 on the Montgomery and Asberg Depression Rating Scale, MADRS), (3) receiving an ineffective antidepressant treatment (a well-conducted treatment at an appropriate dosage for a minimum of 6 weeks), and (4) showing plasma antidepressant levels within the therapeutic range after at least 1 additional week of antidepressant treatment with unchanged dosage. The remitted depressed group will comprise patients: (1) meeting the DSM-5 criteria of MDD diagnosis, (2) achieving remission for at least 8 consecutive weeks according to the standard DSM-5 criteria (as indicated by a MADRS score <10), and (3) receiving antidepressant medications at a stable dosage for 1 week or more. The control group will include normal healthy subjects free from any current or past psychiatric conditions and without peripheral signs of inflammation (as indicated by circulating concentrations of hs-CRP <5 mg/L).

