## Conclusion

Our study′s first objective is to investigate the link between neuroinflammation and clinical severity, as shown earlier by Setiawan (65), and also to target the relationships with certain clinical dimensions such as anhedonia, aboulia, etc. However, the current research aims to assess the effects of antidepressants on neuroinflammation as well as its role in the treatment response. It will help to clarify the putative relationships between neuroinflammation quantified by brain neuroimaging techniques and peripheral markers of inflammation. Finally, it opens innovative and promising therapeutic avenues based on anti-inflammatory strategies for the management of treatment-resistant forms of MDD which are frequently observed in clinical practice. This translational approach is expected to markedly reduce the deleterious impact of MDD on overall functioning, quality of life and economic costs due to the disease.

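### Entry criteria do not support the resistant and responsive group labels, contrasts with controls combine depression with medication, and no contrast identifies an antidepressant effect

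*Protocol article*

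**What the plan says.** All references are to the protocol article.

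- **Labels in the analysis.** Analysis of all data names the three pairwise comparisons as "treatment-resistant MDD vs. control, responsive MDD vs. control, treatment-resistant MDD vs. responsive MDD". Hypothesis (iv), in the Abstract and at the end of the Introduction, makes neuroinflammation a marker of treatment resistance.
- **Definition.** The Introduction notes that definitions vary, then characterises resistance as "the absence of significant symptomatic remission after two successive attempts with antidepressants of different pharmacological classes", with adequate dosage, duration and observance.
- **Entry, currently depressed group.** Eligibility criteria asks for patients "receiving an ineffective antidepressant treatment (a well-conducted treatment at an appropriate dosage for a minimum of 6 weeks", with plasma levels in the therapeutic range after at least one further week at unchanged dosage. Subjects describes them as "treated unsuccessfully with classical antidepressants (SSRIs, SNRIs) before the initiation of a new antidepressant treatment".
- **Entry, remitted group.** Eligibility criteria asks for patients "achieving remission for at least 8 consecutive weeks according to the standard DSM-5 criteria" (MADRS below 10), on a stable dosage for one week or more. Subjects matches them to the currently depressed group on antidepressant class, age and gender.
- **Role of the controls.** Subjects says of the healthy group: "which enables us to control both the depression factor and the treatment factor for the characterization of neuroinflammation". The primary objective in the Introduction states that these volunteers take no antidepressant.
- **Inference claimed.** The Conclusion says "the current research aims to assess the effects of antidepressants on neuroinflammation as well as its role in the treatment response", and the Discussion paragraph of the Abstract says much the same.
- **Measurement.** Table 1 ends at the D7 (± 5 days) assessment visit, which holds the only PET scan.

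**The concern.** The document states three things that its design does not deliver. It analyses a group under a label that its entry criteria do not secure. It says that untreated healthy controls take care of the treatment factor, when they differ from the patients on exactly that factor. It also promises an assessment of antidepressant effects from single scans in non-randomised groups, none of which is depressed and untreated.

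The stake is interpretation. A positive primary result could be reported as the neuroinflammation of depression, or of resistant depression, when medication may contribute and when the patients may have had only one failed treatment. Hypothesis (iv) and the closing claims of the Abstract and Conclusion would then go beyond the data.

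**Working it through.** No planned figure decides this point. The only design figure is 20 per group with 80% power for 12.3 vs. 9.3 ml/cm³. No SD is given with it, so it cannot be reproduced, and nothing below depends on it. The check sets the sections side by side and then asks what each contrast estimates.

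**Step 1: the resistant label.**

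| | Introduction (definition) | Eligibility criteria (entry) |
|---|---|---|
| Failed treatments | 2, successive | 1 |
| Different classes | required | not mentioned |

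No section requires a second failure or a second class. The plural in Subjects, with SSRIs and SNRIs in brackets, names the eligible classes and does not count failures. Recruitment through expert centers for resistant depression is a setting and not a criterion. The number of the 20 patients who meet the Introduction's definition can therefore lie anywhere from 0 to 20. That is the full logical range and not an estimate, since the document gives nothing to narrow it.

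**Step 2: the responsive label.** Entry needs 8 weeks of remission but only one week or more of stable dosage. Nothing requires that remission followed the current drug or dosage. The criteria establish remission under treatment. They do not establish response to that treatment.

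**Step 3: exposure in the primary contrast.** Antidepressant use is 20/20 in the currently depressed group (Eligibility criteria) and 0/20 in the controls (primary objective, and the exclusion of ongoing psychotropic treatment). The indicators for diagnosis and for medication are identical across these 40 subjects. Genotype, the other fixed factor in the primary MANOVA, cannot separate them, and neither could any other covariate.

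**Step 4: what each contrast estimates.** As an illustration, assume additive effects: *h* for having MDD at all, *s* for the current episode, and *t*₁ and *t*₂ for medication in the currently depressed and remitted groups. Let μ be the control mean.

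- Controls: μ
- Remitted: μ + *h* + *t*₂
- Currently depressed: μ + *h* + *s* + *t*₁

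| Contrast | Estimates |
|---|---|
| Currently depressed − control (primary) | *h* + *s* + *t*₁ |
| Remitted − control | *h* + *t*₂ |
| Currently depressed − remitted | *s* + (*t*₁ − *t*₂) |

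A medication term never stands alone. Three group means cannot identify *h*, *s* and a medication effect in addition to μ: even with *t*₁ = *t*₂ there are four unknowns and three means. A group that is depressed and untreated, or a second scan across a change of treatment, would supply the missing information. The design has neither.

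**Step 5: how far matching helps.** In the third contrast medication cancels only if *t*₁ = *t*₂. Matching is on class only. The currently depressed group must show at least 6 weeks of treatment and therapeutic plasma levels, while the remitted group needs one week or more of stable dosage and no plasma criterion. Dose, duration and verified exposure may differ.

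**The case against.** The other side has real weight.

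- **The labels are local.** Resistant and responsive appear as group names in one parenthesis, for the map comparisons. The Abstract, Introduction, Subjects, Eligibility criteria and Outcomes use currently depressed, remitted depressed and control. The primary MANOVA uses diagnosis and genotype. This stands, and it limits severity.
- **The primary contrast is disclosed.** The primary objective says openly that treated patients are compared with untreated volunteers. That stands too, but it does not rescue the sentence in Subjects about controlling the treatment factor. Read kindly, that sentence means a reference group free of both factors. As a statement about inference it is wrong.
- **The useful comparison is already planned.** Currently depressed versus remitted is in the secondary objectives, the secondary outcomes and Analysis of all data. This stands, so nothing new needs to be run.
- **Some wording has charitable readings.** The decrease expected in Subjects can mean a lower level between groups, and controlling the depression factor through the remitted group can mean a shared diagnosis. These are not counted as errors here.

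A reader might go further and infer that all three contrasts confound depression with medication. The documents do not support that: both patient groups are treated and matched on class, so full aliasing is confined to the two contrasts with controls. The opposite inference, that depressed versus remitted holds treatment fixed, is not supported either, because class is all that is matched. A reader might also infer that hypothesis (iv) cannot be examined at all. A cross-sectional association with non-remission under treatment can be examined. What cannot be is resistance as the Introduction defines it, or a causal drug effect.

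**Conclusion.** The concern holds, at moderate severity.

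- The definition of resistance, the entry criterion and the labels in Analysis of all data disagree (two failures against one) and must be reconciled. Which definition is right is not judged here.
- Both contrasts with controls, including the primary one, estimate MDD and medication combined. In the primary contrast the aliasing is complete, 20/20 against 0/20.
- No contrast identifies an antidepressant effect, contrary to the Abstract and Conclusion.

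It would be too strong to say that the primary analysis is invalid or has to change. The primary contrast can be computed and is informative as a combined difference, and the primary outcome, test and sample size are untouched. It would also be too strong to say that the patients are not treatment-resistant: many may be, given where they are recruited, but the criteria do not ensure it.

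The conclusion rests on the stated entry criteria and on Table 1 as the complete visit schedule. The additive model only illustrates the confounding. The aliasing itself follows from the exposure pattern.

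**What to change.** 1. **Analysis of all data:** replace the resistant and responsive labels with the document's own terms, currently depressed and remitted depressed.
2. **Hypothesis (iv):** restate it as an exploratory cross-sectional association with non-remission under treatment, or reconcile it with the Introduction's definition. The second route needs a count of past failed treatments. Enrolment visit lists psychiatric and somatic history and current treatments but does not name past antidepressant trials, so one data item may have to be added.
3. **Subjects:** state that contrasts with controls combine depression and treatment. State also that the planned depressed-versus-remitted contrast is matched on antidepressant class only, and not on dose, duration or verified exposure. Report that contrast beside any depression-specific interpretation of the primary result.
4. **Abstract and Conclusion:** replace the claims about antidepressant effects and about a role in treatment response with wording on cross-sectional association.

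The cost is editing and possibly one data item, with no added scans or patients. The downside is narrower claims.
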